Randomization will be performed centrally by a consultant at the SAS Institute A/S (Copenhagen, Denmark). The allocation sequences will be computer-generated with varying block size, and will be kept unknown to the investigators. Randomization will be stratified by clinical trial site and LT4 treatment duration (<3 months or ≥3 months) and the allocation ratio of intervention and control will be 1:1.

#### **
*Informed consent procedure*
**

Potential participants include all patients with suspected AIT who receive LT4 and are identified at referral or visits to the outpatient clinics or via advertising, as previously described. When AIT is confirmed (serum TPO-Ab ≥ 100 IU/ml, measured within the last 12 months), the patient is invited to an information visit. This visit involves obtaining medical history and written informed consent, blood and urine sampling, and information about trial contact as well as randomization.

#### **
*Concomitant medication or treatment*
**

The trial interventions are given in addition to conventional LT4 treatment. Treatment of the hypothyroidism *per se* will take place at participating clinical trial sites, with LT4 treatment at all clinical trial sites aiming for a serum TSH level within reference ranges, as recommended in local clinical guidelines. Patients are normally followed with blood sampling every 1 to 3 months to adjust LT4 dosage according to TSH levels, as well as visits in the outpatient clinic every 3 to 6 months. Participants in the CATALYST trial will be followed with blood sampling during the trial period, as stated in local clinical guidelines. Participants are advised not to take selenium supplementation in addition to the intervention. A dose of selenium common in multivitamin tablets is, however, allowed and participants are instructed and informed about this upon trial entry, and in the written participant information. The participants’ consumption of additional selenium supplements will be monitored during the trial at specific time points.

#### **
*Monitoring participant adherence to intervention*
**

During the trial, participants self-report their adherence to the intervention at the trial visits (3 months and 12 months after randomization) by stating the number of days a week they take their tablets. Participants will also be instructed to bring remaining tablets and empty containers to the 12 month visit, where they will be counted and registered by an investigator or trial nurse.

#### **

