### Statistical analyses

#### **
*Primary outcome: sample size estimation*
**

The primary outcome is thyroid-related quality of life during 12 months’ intervention, as measured by a composite score from the ThyPRO questionnaire. Sample size estimation is based on this outcome.

The trial should be sufficiently powered to identify a difference between the intervention and the control group of four points on the 0 to 100 ThyPRO composite scale, corresponding to a small to moderate effect. In previously obtained data, the standard deviation of ThyPRO-scores (sigma level) was 20 points [14]. With a correlation between observations on the same participant of 0.50, and a power of 80% and a type I error probability (two-sided α level) of 0.05, a sample size of 236 experimental participants and 236 control participants is required. The sample size estimate is based on a design with five repeated measurements having a compound symmetry covariance structure [51].

#### **
*Secondary outcomes: power estimation*
**

Power calculations are based on serum TPO-Ab concentrations and LT4 dosage. Standard deviations used for power calculations were extracted from unpublished data in a study population of approximately 200 AIT patients from Copenhagen and Odense University Hospitals receiving LT4 treatment [14].

#### **
*Serum TPO-Ab concentration*
**

While a previous study has linked TPO-Ab positivity in hypothyroid patients to impaired HRQL [20], we have not found conclusive evidence in the literature that the level of serum TPO-Ab among participants in this trial, that is, AIT patients with serum TPO-Ab concentration ≥100 IU/ml, has clinical implications. The power estimate is based on a design with three repeated measurements having a compound symmetry covariance structure, with a standard deviation (σ level) of 535 IU/ml (unpublished data) [14], a correlation between observations on the same participant of 0.50, and a type I error probability (two-sided α level) of 0.05. Under these circumstances, a difference in serum TPO-Ab levels of 138 IU/ml between the experimental and control group can be identified with 80% power. We find the power of the trial to assess effect on serum TPO-Ab concentrations acceptable.

#### **
*LT4 dosage*
**

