Analyses will be performed using SAS (SAS Institute Inc. ©, Cary, NC, USA), version 9.3 or later. All analyses will be intention-to-treat analyses performed blinded with the two intervention groups concealed as, for example, ‘A’ and ‘B’. Significance tests will be at the 5% level and two-sided. Table 2 shows, for each outcome, its priority, when it will be measured, the mathematical type of measure, and the analytical procedure to be used when analyzing the outcome values. The analytical procedures and handling of missing values are described next.

**Table 2 T2:** Outcome measures

**Outcome (priority)**	**Times of measurements**	**Mathematical type of quantity (analytical category)**
ThyPRO composite scale score (P)	Time sequence of six measurements^a^	Numerical (1 + 2)
ThyPRO hypothyroid symptoms (S)	Time sequence of six measurements^a^	Numerical (1 + 2)
ThyPRO goitre symptoms (S)	Time sequence of six measurements^a^	Numerical (1 + 2)
LT4 dosage (S)	Time sequence of four measurements^b^	Numerical (1 + 2)
Serum TPO-Ab (S)	Time sequence of four measurements^b^	Numerical (1 + 2)
Serum FT3/FT4 Ratio (S)	Time sequence of four measurements^b^	Numerical (1 + 2)
Plasma selenium (S)	Time sequence of four measurements^b^	Numerical (1 + 2)
Biomarkers of immunology and oxidative stress (S)	Time sequence of four measurements^b^	Numerical (1 + 2)
Adverse reactions (S)	End of trial	Rate (3)
Serious adverse events (S)	End of trial	Rate (3)

Outcomes with priorities, times of measurement and mathematical types of quantity with analytical categories. P, primary outcome measure; S, secondary outcome measure. Analytical categories 1 to 3 are defined in the main text. ^a^, includes five measurements relative to the reference time (6 weeks, 3 months, 6 months, 12 months and 18 months after randomization); ^b^, includes three measurements relative to the reference time (3 months, 12 months and 18 months after randomization).

#### **
*Analytical procedures*
**

Depending on the specific analytical category of each outcome measure, one or two of three types of regression analyses will be applied (Table 2).

#### **
*Analytical categories*
**

*Type 1* includes a continuous outcome measure (*y*) measured 3 to 6 times at 6 weeks, 3, 6, 12 or 18 months after randomization. It is viewed as a linear function of time (*t*). The model is:

*y* = *a* + *b***I* + *c***t* + *d***I***t*

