Depending on the mean value structure in the two groups, this model may be enhanced to include a second- or third-degree polynomial. *I* is the intervention indicator, and *a*, *b*, *c* and *d* are the coefficients of the regression equation. A mixed model with repeated measures will be used. An unstructured covariance matrix will be used. In the case of lack of convergence, the following covariance structures will be tried in the specified order: the spatial power law and the compound symmetric.

*Type 2* includes a single continuous outcome measure. The general linear univariate model will be used. As a sensitivity analysis, a nonparametric test (Mann Whitney) will be conducted and the result discussed.

*Type 3* includes a count of events within a specified period of counting as outcome measure. The generalized linear model will be used with the Poisson distribution, link = log and log (period) as offset. As a sensitivity analysis a nonparametric test (Mann Whitney) is conducted to compare the distributions of rates between the groups and the result discussed.

#### **
*Missing values*
**

If the distributions of the primary outcome measure differ significantly between the two intervention groups, multiple imputations (MI) will be used to replace missing data with substituted values using SAS version 9.3 or later. In the MI analysis, the model variables and additional variables significantly related to the variables with missing values of these variables will be used. Ten imputed data sets will be produced.

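### Adverse reaction and serious adverse event rates are compared with a Poisson model for which no overdispersion-robust variance is stated; if events cluster within participants, the rate-ratio intervals may be too narrow

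*Protocol article*

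**What the plan says.** Table 2 of the protocol article classes adverse reactions and serious adverse events as secondary outcomes, analysed as rates in category 3. The Analytical categories subsection defines that category as one that "includes a count of events within a specified period of counting as outcome measure". The model is fixed by family, link and offset: "The generalized linear model will be used with the Poisson distribution, link = log and log (period) as offset". The next sentence adds a check: "As a sensitivity analysis a nonparametric test (Mann Whitney) is conducted to compare the distributions of rates between the groups", with its result to be discussed.

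On testing, the Data analyses subsection says: "Significance tests will be at the 5% level and two-sided". Serious events are to be found mainly from registry data on admissions and deaths (Assessment of adverse reactions and events). Table 1 has participants asked about adverse reactions at 3, 12 and 18 months.

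Nothing is said about the variance of the Type 3 estimate beyond the choice of the Poisson family.

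**The concern.** A Poisson model takes the variance of each participant's count to equal its mean. That fails when some participants are more prone to events than others. Registry admissions are an obvious candidate, since one person can be admitted repeatedly. The trial also mixes newly diagnosed and established patients, adults of any age and four sites, and no covariates are named for Type 3. Adverse reactions might cluster too, but the article does not say whether a complaint that persists across visits counts once or several times.

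If counts are overdispersed, the estimated rate ratio is still sound but its model-based standard error is too small. The interval around a harm estimate then claims more precision than the data carry, and the Poisson test rejects too often in either direction. The Mann-Whitney test does not rely on the Poisson variance, but it yields neither a rate ratio nor an interval. The interval reported for harms would therefore still come from the Poisson fit.

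**Working it through.** **Is there a figure to reproduce?** The article gives no safety rate, dispersion, interval width or power for safety, so there is none for this point. The group size used below does reproduce: 2 × (20 × (1.960 + 0.842) / 4)² × (1 + 4 × 0.5)/5 = 392.4 × 0.6 = 235.5, hence 236 per group.

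**Inputs from the article.** 236 per group, 1:1 allocation, two-sided 5%. The only event count is in the Safety section: 12 adverse events and no serious ones among 501 participants in an earlier trial of the same tablets, so 12/501 = 0.024 per participant. The same section puts common reactions at 1% to 10%.

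**Assumed inputs.** All mean counts other than 0.024, and every dispersion value. Counts are taken as gamma-Poisson with mean μ and frailty variance k, and follow-up as equal for everyone.

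**Formulas.** Variance/mean φ = 1 + kμ. True SE of the log rate ratio = Poisson SE × √φ. Coverage of a nominal 95% Poisson interval ≈ 2Φ(1.96/√φ) − 1.

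For φ = 1.2, 1.5 and 2.0 these give type I error of 7.4%, 11.0% and 16.6%, and correct intervals 10%, 22% and 41% wider on the log scale.

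**Simulation under no treatment effect.** 236 per group; 10,000 runs for the Poisson and Pearson-scaled Poisson tests, 2,000 for Mann-Whitney. Runs with no events in one group were dropped.

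| μ | k | SE ratio √φ | Coverage (formula) | Poisson error | Scaled Poisson error | Mann-Whitney error |
|---|---|---|---|---|---|---|
| 0.024 | 1 | 1.01 | 94.7% | 2.4% | 2.2% | 4.5% |
| 0.024 | 4 | 1.05 | 93.9% | 3.0% | 2.0% | 3.6% |
| 0.1 | 0 | 1.00 | 95.0% | 4.8% | 5.0% | 6.4% |
| 0.1 | 1 | 1.05 | 93.8% | 5.7% | 4.8% | 5.4% |
| 0.1 | 4 | 1.18 | 90.2% | 9.2% | 4.8% | 4.7% |
| 0.3 | 0 | 1.00 | 95.0% | 5.0% | 5.1% | 5.4% |
| 0.3 | 1 | 1.14 | 91.4% | 8.4% | 4.9% | 4.8% |
| 0.3 | 2 | 1.26 | 87.9% | 12.3% | 5.1% | 4.3% |
| 0.3 | 4 | 1.48 | 81.4% | 18.9% | 5.3% | 5.2% |
| 1.0 | 2 | 1.73 | 74.2% | 25.9% | 5.2% | 5.7% |

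At μ = 0.024 only about 236 × 0.024 = 5.7 events per group are expected, and the Poisson test falls below its nominal level.

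**What this does to an interval.** Take μ = 0.3 and k = 2. Expected events per group are 236 × 0.3 = 70.8. The Poisson SE is √(2/70.8) = 0.168, so an estimated ratio of 1 carries an interval of 0.72 to 1.39. With φ = 1.6 the SE is √(3.2/70.8) = 0.213 and the interval is 0.66 to 1.52.

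**Does the remedy work?** Scaling by the Pearson statistic brought type I error to 4.8% to 5.3% wherever μ was at least 0.1. A separate simulation with robust standard errors (3,000 runs per setting, μ from 0.1 to 1) gave 4.9% to 5.6%, where plain Poisson gave 7% to 17%. Negative binomial regression was not simulated.

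**The case against.** The strongest reply is that handling of dispersion is usually left to a statistical analysis plan, which is not at hand, and that sandwich standard errors would be compatible with the quoted model sentence. That limits the severity. It does not remove the point, because the article goes beyond naming a general approach: it fixes family, link and offset. It also gives an ordered fallback for the covariance structure in Type 1 and no counterpart for the variance in Type 3.

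A reader might infer that the plan makes no allowance at all for non-Poisson counts. The article does not support that. The Mann-Whitney comparison is a real safeguard for the test, with simulated type I error of 3.6% to 6.4% in every scenario. A false signal from the Poisson test could be exposed by it. What it leaves open is the interval.

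A reader might also infer that the intervals are bound to be too narrow. That is not supported either. The article reports no dispersion, and at the one event rate it allows to be derived there is no excess error. At that rate a variance/mean ratio of 1.2 would need k of about 0.2/0.024 = 8, and a ratio of 2.0 about 1/0.024 = 42, which is extreme clustering. Against this, the earlier trial recorded no serious events and is described over 6 months of supplementation. It therefore says little about registry admissions over up to 18 months.

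Finally, both outcomes are secondary, no stopping rule in the article rests on these intervals, and every serious event is to be reported in any case. All of this stands and keeps the point minor.

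**Conclusion.** The point holds conditionally. As stated, the Type 3 model gives correct intervals only if counts are close to Poisson. If events cluster within participants, the rate-ratio intervals may be too narrow, and the sensitivity test does not supply a corrected one.

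The effect is negligible at about 0.024 events per participant. It becomes material at about 0.1 with strong clustering (coverage about 90% at k = 4) and at 0.3 and above (coverage about 91% to 81% for k from 1 to 4). These figures rest on assumed dispersion, assumed means other than 0.024, and equal follow-up. If adverse reactions are as rare as in the earlier trial, the point concerns mainly serious adverse events. Severity is minor.

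**What to change.** Keep the log link and the offset for time at risk. Before unblinding, prespecify one of two options as the Type 3 analysis: the same Poisson model with robust (sandwich) standard errors, or negative binomial regression. Do not leave the choice until the dispersion has been seen. Retain Mann-Whitney as the sensitivity test.

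The cost is about one line of analysis text. Intervals become somewhat wider if the counts are overdispersed and are practically unchanged if they are not.

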### Ethical considerations

As specified by the Danish Medicines Agency, the CATALYST trial is not subject under the Danish Medicines Act (law 1180 by 12/12/2005, §88, section 1). The CATALYST trial obeys the rules and regulations set down by The Biomedical Research Ethics Committees, Danish Data Protection Agency, and the health authorities. The CATALYST trial will be conducted in accordance with the Declaration of Helsinki. The trial has been approved by the Regional Scientific Ethical Committees for Southern Denmark (project ID: S-20130123).

## Discussion

The data available from previous trials warrant further investigation, since a benefit from selenium supplementation is still unproven in patients with AIT. In previous trials of intervention with selenium in patients with AIT, effect on serum TPO-Ab concentration has been the primary outcome. Intervention durations of 3, 6, 9, and 12 months using different selenium formulations have shown positive effects on serum TPO-Ab concentrations. This trial will be the largest yet, with 472 participants, and the first to measure changes in quality of life, by ThyPRO, as the primary outcome. The sample size estimate does not take dropouts or off-trial use of selenium supplements into account. Plasma selenium concentrations will be measured to assess selenium intake during the trial. Importantly, utilizing the ThyPRO questionnaire will enable us to determine how selenium supplementation may affect specific aspects of thyroid-related quality of life in AIT patients. In assessing quality of life, the effect of levothyroxine alone will be taken into account by adjusting for TSH levels. Choosing a 12-month intervention period allows for a time sequence of five measurements. The 6-month postintervention follow-up period was added to assess sustained effects. This trial will also look into selenium’s mechanisms of action in AIT, by measuring biomarkers of immunological activity, and will be the first to evaluate whether selenium supplementation affects LT4 dosage. Dosage reduction is of clinical interest and discontinuation of LT4 would be of direct clinical relevance. An effect of selenium supplementation on LT4 dosage is conceivable, owing to upregulation of selenoproteins involved in thyroid hormone synthesis or thyrocyte protection.

Participants will be stratified for LT4 treatment duration of more or less than three months, corresponding to newly diagnosed and established patients, respectively. Participants in the newly diagnosed patient group will respond to LT4 treatment *per se*, in terms of restoration of euthyroidism, while the established patient group will not experience major fluctuation in the thyroid hormone levels during the study period. The stratification also allows an investigation of whether the newly diagnosed and established patient groups respond differently to selenium supplementation. This investigation will, however, be strictly exploratory, as it is likely to be underpowered.

It is of major importance to the CATALYST trial’s initiators that the results will be as directly applicable to daily clinical practice as possible. Therefore, it will be conducted as a pragmatic trial [52], with participating patients following their usual treatment at their usual hospitals in the care of whichever physician is involved. At the same time, it is a priority to collect high-quality data with respect to HRQL, since this is the primary outcome of the trial.

The intent of conducting a pragmatic trial, while still measuring HRQL meticulously, presents a challenge. Considerable effort has therefore been directed at designing a trial data management system that can handle distance from participants and maintain close monitoring [45]. The system initiates and keeps track of patient-reported outcomes and identifies a need for trial personnel input and action. The system also identifies the site of the information provider and LT4 treatment duration of new participants, in order to deliver randomization numbers. Meticulous follow-up of missing responses to the HRQL measurements is incorporated into the system, to minimize the well-known problem with missing HRQL data in clinical trials.

The intent to comply with the ICH-GCP guidelines is also a challenge when conducting a pragmatic trial. In the CATALYST trial, the experimental intervention is a dietary supplement rather than a drug. The need to monitor adverse reactions and events is addressed by a combination of thorough instruction of the participants to contact their trial person in case of symptoms indicative of adverse reactions or events, surveillance of patients’ responses to prompts through the trial data management system and integration with national databases regarding hospitalizations.

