Selenium is a nonmetal mineral, a trace element and an essential micronutrient, incorporated into selenoproteins as the 21st amino-acid, selenocysteine. Selenoproteins have a wide range of effects in, for example, redox homeostasis, immunity, reproduction and thyroid hormone metabolism [22]. The recommended daily selenium intake in Denmark is 50 μg and 40 μg for men and women, respectively, and it is believed that 10% of Danish adults would benefit from increasing their intake [23]. In a recent Danish study, serum selenium concentration was inversely associated with thyroid volume, supporting a role for selenium in the thyroid gland, which indeed has the highest selenium concentration of all tissues [22,24]. A number of selenoproteins are expressed in thyrocytes. The most important of these are the iodothyronine deiodinases (DIO1, DIO2) that catalyze the formation of T3 from T4, and the glutathione peroxidases (GPx1, GPx3, GPx4) that catalyze the removal of peroxides and protect the thyrocytes from oxidative stress [25]. Two randomized clinical trials have shown no effect of selenium supplementation on serum TSH and thyroid hormone concentrations in healthy adults, even in those with moderately deficient selenium status [26,27]. Meanwhile, in the majority of 13 randomized clinical trials, selenium, in various formulations, effectively decreased serum TPO-Ab concentrations in AIT patients [28-40]. Some of the trials also reported other beneficial effects, including improvements in quality of life, although with limited presentation of the data supporting this claim. However, a recent systematic review concluded that evidence to support or discard the efficacy of selenium supplementation in AIT patients is inadequate, and highlights the need of additional randomized placebo-controlled trials to investigate direct clinical outcomes, in order to aid clinical decision making [41].

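### The Discussion promises a TSH adjustment of quality of life that the primary model does not contain; if on-trial TSH is meant, it can bias the estimate away from the intention-to-treat effect

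*Protocol article*

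**What the plan says.** The Discussion of the protocol article states: "In assessing quality of life, the effect of levothyroxine alone will be taken into account by adjusting for TSH levels". It names no time point for TSH and does not say whether the adjusted analysis is primary or supportive.

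The section on Analytical categories writes out the Type 1 model, which Table 2 assigns to the ThyPRO composite score: y = a + b·I + c·t + d·I·t. Of the outcome it says "It is viewed as a linear function of time". The only extension of the mean structure is in time: "this model may be enhanced to include a second- or third-degree polynomial". TSH does not appear. The Data analyses section declares every analysis intention-to-treat.

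Two other places bear on how TSH behaves after randomisation. Under Concomitant medication, treatment is described "with LT4 treatment at all clinical trial sites aiming for a serum TSH level within reference ranges", and "Patients are normally followed with blood sampling every 1 to 3 months to adjust LT4 dosage according to TSH levels". The Discussion adds: "An effect of selenium supplementation on LT4 dosage is conceivable, owing to upregulation of selenoproteins involved in thyroid hormone synthesis or thyrocyte protection".

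**The concern.** The stated reason for the adjustment is to separate out what LT4 does by itself. The paragraph that follows in the Discussion expects newly diagnosed patients, planned as half of the sample, to respond to LT4 during the trial. Only TSH measured on trial tracks that response, so on-trial TSH is the more natural reading.

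On-trial TSH is not a baseline covariate. It follows allocation, it is tied to LT4 titration, and selenium may move it. Conditioning on it can do two things. It can block any part of a benefit that runs through thyroid function. It can also induce an association between arm and unmeasured influences shared by TSH and quality of life. Either way, the coefficient for intervention no longer estimates the full effect of adding selenium to LT4, which is the trial's hypothesis.

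Nor is the adjustment needed for its stated purpose. Randomisation, stratified by LT4 duration, already balances the response to LT4 itself in expectation.

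At stake is which coefficient answers the primary question. An analyst cannot follow both the Discussion sentence and the written model in one analysis.

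**Working it through.** **1. The plan's own figure.** Inputs from the sample size section: difference 4 points, SD 20, within-participant correlation 0.50, five measurements with compound symmetry, two-sided α 0.05, power 80%, 1:1 allocation.

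- Variance of the mean of five scores: 20² × (1 + 4 × 0.5)/5 = 400 × 0.6 = 240, so the effective SD is 15.49.
- n per arm = 2 × (1.960 + 0.842)² × 240/4² ≈ 235.5, rounded up to 236. This agrees with the plan.
- Power at 236 per arm = Φ(4/√(2 × 240/236) − 1.96) = Φ(2.805 − 1.96) = 80.1%.

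The planned size thus matches a model without TSH.

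**2. Which TSH, and when.** From Table 1:

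| | Baseline | 6 weeks | 3 months | 6 months | 12 months | 18 months |
|---|---|---|---|---|---|---|
| ThyPRO | yes | yes | yes | yes | yes | yes |
| TSH | yes | no | yes | no | yes | yes |

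Two of the four ThyPRO assessments between baseline and the end of treatment (6 weeks and 6 months) have no scheduled TSH beside them.

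**3. If a share f of the effect were removed.** The share is an assumption; the document gives none. With residual variance held fixed, power = Φ(4(1 − f)/√(2 × 240/236) − 1.96):

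| f | Effect estimated | Power at 236 per arm |
|---|---|---|
| 0 | 4.0 | 80% |
| 10% | 3.6 | 71% |
| 25% | 3.0 | 56% |
| 50% | 2.0 | 29% |

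**4. What would have to be true for a loss to arise.** Assume that quality of life worsens by 0.3 SD per SD of TSH and that selenium lowers TSH by *a* SD. The adjusted effect is then 4 − 0.3 × 15.49 × *a*:

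- *a* = 0: 4.0 points, no loss.
- *a* = 0.1: 4 − 0.46 = 3.5.
- *a* = 0.2: 4 − 0.93 = 3.1.
- *a* = 0.3: 4 − 1.39 = 2.6.

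Now add an unmeasured cause with a loading of 0.5 on both TSH and quality of life. At *a* = 0.2 this takes off a further 0.2 × 0.5 × 0.5 × 15.49 = 0.77, leaving 2.3 points. If TSH itself has no effect on quality of life but shares that cause, the estimate is still about 3.2. Simulated data under the same assumptions gave matching values. Both terms are proportional to *a*: without a shift in TSH, neither bias arises.

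**5. If the unmatched scores were dropped.** Four scores: variance 400 × (1 + 3 × 0.5)/4 = 250, power 78.5%. Two scores: variance 400 × (1 + 0.5)/2 = 300, power Φ(4/√(2 × 300/236) − 1.96) = Φ(2.509 − 1.96) = 71%. This is a limit that applies only if no other TSH value is used at those times.

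**The case against.** A reader might infer that the primary result will be adjusted for on-trial TSH and that the trial will therefore lose its planned power. The document does not support that, for several reasons.

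- The sentence names no time point. TSH is also measured at baseline, and adjusting for that value would be harmless. On-trial TSH is an inference from the stated purpose, though a reasonable one.
- The written primary model is already unadjusted. If the analysis section governs, the TSH model is an additional analysis. The printed equation may also be schematic, since it omits the stratification factors too, and an article may leave the covariate list to the analysis plan.
- The Background reports that "Two randomized clinical trials have shown no effect of selenium supplementation on serum TSH and thyroid hormone concentrations in healthy adults". Those were healthy adults, not LT4-treated patients with thyroiditis, so this carries over only in part.
- Because LT4 is titrated to the same TSH target in both arms, a changed need for LT4 would tend to show as a different dose rather than a different TSH. A conceivable effect on dose is not evidence of a shift in TSH.
- The shares in step 3 are arbitrary. TSH might also explain outcome variance in newly treated patients, which would work in favour of power.
- Routine samples, normally taken every 1 to 3 months and fed into the electronic case report forms, might fill some of the gaps at 6 weeks and 6 months.

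All of this limits the size and certainty of the harm. It does not remove the mismatch: the article says that quality of life will be adjusted for TSH, gives a model without TSH, and does not say how the two relate.

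**Conclusion.** The point stands as an unresolved statement about the primary outcome that carries a risk of bias. The Discussion and the written model do not describe the same analysis. On the likelier reading of the Discussion, the adjusting variable is measured after randomisation, and conditioning on it can move the estimate away from the intention-to-treat effect.

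The size cannot be derived from the document. It is zero if selenium does not shift TSH, and it may be small given titration and the cited null findings. The fall from 80% to 71% for a 10% loss, and the larger falls in the table, illustrate sensitivity; they are not expected consequences. The drop from 78.5% to 71% for two scores instead of four likewise assumes that no routine TSH value is used. The planned 236 per arm is correct for the unadjusted model and needs no change.

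**What to change.** State in the analysis section that the primary ThyPRO analysis is not adjusted for any TSH measured after randomisation, as the written model already implies. If covariate adjustment is wanted, name baseline TSH and the stratification factors (site and LT4 duration). Reword the Discussion sentence to match, and label any model that includes on-trial TSH as exploratory, saying which TSH values are used at 6 weeks and 6 months.

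The cost is about one sentence in each of the two sections, settled before the data are analysed. No change to sample size or data collection follows.
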